### Sample size

This trial is a cohort study. The sample size is calculated by relative risk (RR). Referring to recent two cohort studies, in a total of 112,018 healthy people, the 10-month MACE rate was 0.05% [15], another study showed that 1 year MACE in ACS patients is 8.1%(151 of 1864) [16]. The sample size is 125 people calculating by PASS software. Considering the 10% loss rate of follow-up and in order to improve reliability and reduce sampling error, we plan to enroll 150 ACS patients in total, including 50 STEMI, 50 non-STEMI and 50 UA patients.

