## Abstract

**Background:**

Acute coronary syndrome(ACS) is the leading cause of mortality and disability worldwide. Immune response has been confirmed to play a vital role in the occurrence and development of ACS. The objective of this prospective, multicenter, observational study is to define immune response and their relationship to the occurrence and progressive of ACS.

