## Methods

### Aim of the study

To detect the characteristics of various subtypes of monocytes, macrophages, T cells and explore the expression of CD47, sirpα,S100A4 and Tim-3 on these cells in peripheral blood of ACS patients and investigate the relationship between them and the occurrence of MACE 1 year later.

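### The only justification for 125/150 patients compares MACE in healthy people with MACE in ACS patients, a contrast this ACS-only cohort does not make, so the aim of relating immune markers to MACE within ACS has no power justification

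*Protocol article*

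**What the plan says.** The Sample size section of the protocol article bases the calculation on a relative risk and gives two external rates. The first is "in a total of 112,018 healthy people, the 10-month MACE rate was 0.05"%. The second is "1 year MACE in ACS patients is 8.1%(151 of 1864"). From these it states "The sample size is 125 people calculating by PASS software". It then allows for loss ("Considering the 10% loss rate of follow-up") and arrives at the enrolment target: "we plan to enroll 150 ACS patients in total, including 50 STEMI, 50 non-STEMI and 50 UA patients".

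The Study populations and Inclusion criteria sections admit only patients with ACS, and the inclusion criteria also require PCI. No healthy or other non-ACS group is described. The Aim of the study is to measure immune-cell subsets and markers in ACS patients and "investigate the relationship between them and the occurrence of MACE 1 year later". The Statistical analysis section plans univariate tests, stepwise logistic regression on the significant indicators, and ROC analysis.

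For the sample size itself, the section gives no power, sidedness, allocation ratio or test, and no marker effect or event rate by marker level.

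**The concern.** A sample-size calculation should describe the comparison the study will make. This one describes how much more often MACE occurs in ACS patients than in healthy people. The study will instead compare marker levels between ACS patients who have MACE and ACS patients who do not. The information for that comparison comes from the number of MACE within the cohort, and the section neither states nor uses that number.

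At stake is how the results are read. A reader who sees a software-derived figure with a loss allowance will take 150 as powered for the marker question. If a marker then shows no association, that may be read as evidence against it, when the study may have been able to detect only a large difference. A cut-off or AUC may likewise be given more weight than its precision supports.

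**Working it through.** **Step 1: reproduce the stated 125.** Inputs from the Sample size section: p1 = 0.081 and p2 = 0.0005, so the implied RR is 0.081/0.0005 = 162. As a check on the ACS rate, 151/1864 = 8.10%. Assumed, because not stated: two-sided 5%, 1:1 allocation, pooled two-proportion test without continuity correction.

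n per group = [z(0.975)·√(2p̄(1−p̄)) + z(power)·√(p1(1−p1) + p2(1−p2))]² / (p1−p2)²

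Here p̄ = 0.04075, 2p̄(1−p̄) = 0.07818, p1(1−p1) + p2(1−p2) = 0.07494, and (p1−p2)² = 0.00648.

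| Power | n per group |
|---|---|
| 80% | 93.5 |
| 90% | (0.5480 + 0.3508)²/0.00648 = 124.7, rounded up to 125 |
| 95% | 153.8 |

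So 125 is matched exactly as a per-group size at 90% power (250 over two groups). No 1:1 variant tried gave 125 as a two-group total; the smallest such total was 144. The match is not unique: a one-sided 5% test at 95% power with unpooled variance gives 125.1 per group. A one-sample test against a fixed 0.05% would need only about 11 to 37.

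**Step 2: check the loss allowance.** 125/0.90 = 138.9, so 139. The planned 150 covers it. This part is sound.

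**Step 3: what 150 delivers for the stated aim.** Evaluable patients: 150 × 0.90 = 135. Expected MACE at 8.1%: 135 × 0.081 = 10.9, about 11, with a 95% binomial range of 5 to 18. By ACS type: 50 × 0.081 = 4.1 if all are followed, or 45 × 0.081 = 3.6 after loss.

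*Detectable marker difference* (one marker, two-sample t-test, two-sided 5%, 80% power). Normal approximation: d = (1.960 + 0.842)·√(1/n₁ + 1/n₂). With 11 and 124 this is 2.802 × 0.3146 = 0.88; the t distribution gives 0.89. Power for a difference of 0.5 SD is about 35%.

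*Precision of an AUC of 0.70* (Hanley–McNeil). Q1 = 0.7/1.3 = 0.5385 and Q2 = 0.98/1.7 = 0.5765.

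SE = √{[0.21 + 10(0.5385 − 0.49) + 123(0.5765 − 0.49)]/(11 × 124)} = √(11.33/1364) = 0.091

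95% interval: 0.70 ± 1.96 × 0.091 = 0.52 to 0.88.

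**Step 4: vary the event rate.** The 20% and 30% rates are assumptions; 8.1% is the only ACS rate in the document.

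| MACE rate | Events in 135 | Detectable difference (80% power) | 95% interval for AUC 0.70 |
|---|---|---|---|
| 8.1% (protocol) | about 11 | 0.89 SD | 0.52 to 0.88 |
| 20% (assumed) | 135 × 0.20 = 27 | 0.61 SD | 0.58 to 0.82 |
| 30% (assumed) | 135 × 0.30 = 40.5, taken as 40 | 0.53 SD | 0.60 to 0.80 |

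These figures are for a single pre-chosen marker, with no allowance for screening several markers or for stepwise selection.

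**The case against.** The strongest reply concerns the event rate. The MACE definition behind the published 8.1% is not visible here, and this protocol's composite includes symptom-defined recurrent angina and heart failure, so its rate could be higher. Power rises quickly if it is. For a marker split at its median (an illustration, not a planned analysis), power to detect RR 3 with 135 patients is 41% at 8.1%, 69% at 15%, 84% at 20% and 97% at 30%. This stands, and it is why a range has to be shown. It does not rescue the calculation, because a higher rate would not make the healthy group relevant.

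Some stronger readings are tempting but not supported:

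- **That 125 is half of a 250-person design presented as a total.** The section states neither power, sidedness nor allocation, and other settings also give about 125. It does not call 125 a two-group total; its total is the 150 ACS patients. The exact match suggests that 125 is the ACS arm of a two-group comparison but does not prove it, and the point does not depend on it.
- **That the study has no power.** What is missing is a power justification. At 8.1% the power for moderate marker differences is low, not zero.
- **That any null result would be uninformative.** That depends on the event rate and on the size of effect considered.
- **That the unequal periods of the two rates (10 months and 1 year) distort the figure.** Scaling 0.05% to 12 months gives 0.06% and a per-group size of 125.1 instead of 124.7, which is immaterial.

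The Abstract's looser objective, to "define immune response and their relationship to the occurrence and progressive of ACS", is a separate matter of wording. The Aim of the study confines the question to MACE in ACS patients, and the abstract sentence has no bearing on 125.

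A statistical analysis plan might add detail, but this is not an omission. The article states a calculation whose basis does not fit the design in the same article.

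**Conclusion.** The point holds. The sole stated basis for 125/150 is a comparison with healthy people that the cohort does not contain, so the number is not justified for relating immune markers to one-year MACE within ACS. The fault is a mismatched contrast: the stated rates do yield 125 under common settings, and the loss allowance is adequate.

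Its size depends on the event rate. At the protocol's 8.1%, the cohort can be expected to yield about 11 MACE, detect only a large marker difference (about 0.89 SD), and estimate a moderate AUC with an interval that nearly reaches 0.5. At an assumed 20% to 30% it can detect about 0.61 to 0.53 SD. These results assume 10% loss, one marker, two-sided 5% and 80% power. At 8.1%, about 4 events per ACS type are too few for more than exploratory analysis.

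**What to change.** In the Sample size section, delete the healthy-versus-ACS calculation and keep 150 as the enrolment target. Replace it with what 150 delivers for the within-ACS aim:

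- expected MACE among 135 evaluable patients at 8.1% (about 11, 95% range 5 to 18) and at higher rates labelled as assumptions, such as 20% (27) and 30% (about 40);
- the marker difference detectable with 80% power at two-sided 5% at each rate (0.89, 0.61 and 0.53 SD);
- the expected 95% interval for an AUC of 0.70 (0.52 to 0.88 at 8.1%, 0.58 to 0.82 at 20%).

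State that these are single-marker figures. Describe the prediction analyses and the analyses by ACS type as exploratory.

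The cost is rewording. No patients, visits or procedures change. The downside is that the stated justification becomes less favourable than the present text suggests.

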### Statistical analysis

The counting data were expressed as percentage and analyzed by χ2 test and non-parametric rank sum test. The measurement data were expressed as mean ± SD deviation. Student’s t-test was used for comparison of indicators. and P < 0.05 was considered statistically significant. Multivariate logistic stepwise regression analysis was performed on the statistically significant indicators to screen out the predictors of target outcomes. The receiver operating characteristic (ROC) analysis was used to analyze the selected predictors. The optimal cut-off point was found when the incidence of MACE was lowest by calculating the area, sensitivity and specificity under the curve, the optimal cut-off point was found when the incidence of MACE was lowest. The results were analyzed and discussed, the rationality of the results was analyzed in combination with the clinical practice and related literature, and the results were expected to have certain guiding significance for clinical work.

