**Methods:**

This is a multicenter, prospective, observational longitudinal cohort study. The primary outcome is the incidence of major adverse cardiovascular events (MACE) including in-stent restenosis, severe ventricular arrhythmia, heart failure, recurrent angina pectoris, and sudden cardiac death, and stroke one year later after ACS. Demographic characteristics, clinical data, treatments, and outcomes are collected by local investigators. Furthermore, freshly processed samples will be stained and assessed by flow cytometry. The expression of S100A4, CD47, SIRPα and Tim-3 on monocytes, macrophages and T cells in ACS patients were collected. Follow-up: during hospitalization, 3, 6 and 12 months after discharge.

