#### Blood sample and data collection

Peripheral blood samples of these patients were obtained within 24 h of admission and collected in heparin anticoagulant tube (2–4 mL). Samples were placed at room temperature for testing within 24 h. Clinical data of patients such as age, gender, history of hypertension, coronary heart disease and diabetes mellitus, body mass index (BMI), white blood cell count, level of hemoglobin, platelet, creatinine, aspartate aminotransferase (AST), alanine aminotransferase (ALT), lipid profile, left ventricular ejection fraction, left ventricular end-diastolic volume etc. were collected. The results of coronary angiography were recorded as well.

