Our previous study found that expression of S100A4 elevated in peripheral leukocyte of ACS patients. S100A4 is a polypeptide protein, mainly composed of 101 amino acids, belonging to the S100 protein family, in which there are a total of 21 identified members, and it is also one of the largest subfamilies of calcium ion binding protein family [12]. Studies have shown that S100A4 protein can promote tumor invasion and metastasis, regulating a variety of cell functions. When combined with calcium ion, S100A4 protein is a crucial key to differentiation, proliferation of cells, muscle contraction, inflammatory and apoptosis through the pathway of calcium ion signal transduction [38–40]. A study has shown that the level of S100A4 will increase in ACS patients, which may become a new biomarker to predict ACS [41]. S100A4 knockout can aggravate ventricular remodeling, myocardial fibrosis, and distal myocardial capillary density reduction in mice [42]. Whether elevation of S100A4 affects the prognosis of ACS patients is unknown yet.

In this study, we assume that the characteristics of various subtypes of monocytes, macrophages, T cells and the expression of CD47, sirpα and S100A4 on these cells in peripheral blood differs in ACS patients and will affect the prognosis of these patients, so this protocol were set to detect the account and distribution of classical monocytes, non-classical monocytes, intermediate monocytes, M1 type macrophages, M2 type macrophages, CD4 positive T cells, CD8 positive cells and NKT cells and the level of CD47, sirpα, tim-3 and S100A4 by detecting different surface markers through flow cytometry. Then primary outcomes are observed during hospitalization and 3,6 and 12 months after discharge of participants. It is expected that this study will reveal the possible targets to improve the prognosis or prevent from occurrence of MACE. Since it’s a multicenter study, the enrollment rate of participants will be accelerated and it can ensure that the collected data are more symbolic and improve the richness and credibility of the test basis. We will use the SPIRIT checklist to improve the quality of the study.

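### Screening many immune indicators at unadjusted P<0.05, then stepwise logistic regression and ROC in the same patients, is likely to report false predictors with an optimistic AUC even if no marker works

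*Protocol article*

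**What the plan says.** The Statistical analysis section of the protocol article sets out a chain of four steps.

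1. Comparison of indicators: "Student’s t-test was used for comparison of indicators", with χ² and rank sum tests for counts, and "P < 0.05 was considered statistically significant".
2. Selection: "Multivariate logistic stepwise regression analysis was performed on the statistically significant indicators to screen out the predictors of target outcomes".
3. Performance: "The receiver operating characteristic (ROC) analysis was used to analyze the selected predictors".
4. An optimal cut-off is then read from the ROC analysis.

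The candidates are described elsewhere. The Discussion lists "classical monocytes, non-classical monocytes, intermediate monocytes, M1 type macrophages, M2 type macrophages, CD4 positive T cells, CD8 positive cells and NKT cells", together with "the level of CD47, sirpα, tim-3 and S100A4 by detecting different surface markers through flow cytometry". The abstract's Methods paragraph speaks of "The expression of S100A4, CD47, SIRPα and Tim-3 on monocytes, macrophages and T cells", so the molecules are measured on the cell types. Blood sample and data collection adds clinical, laboratory and echocardiographic variables (15 named items, counting the lipid profile once) and the angiography findings. No total number of indicators is given.

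The Sample size section plans 150 ACS patients, allows 10% loss to follow-up and cites a one-year MACE rate of 8.1% in ACS. It describes one cohort and no validation sample.

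**The concern.** Each step uses the same outcomes in the same patients. Many tests at 0.05 pass some indicators by chance. The stepwise step keeps those that fit the observed events best, and the ROC then measures discrimination in the data that chose them. The resulting AUC, sensitivity, specificity and cut-off are biased upward, and the bias grows as events become few relative to candidates.

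This is the only analysis the article states for linking the immune indicators to MACE, which is the study's aim. The article also expects to identify possible targets and to offer some guidance for clinical work. If the procedure usually returns a predictive model when nothing is predictive, a positive report carries little information and may not replicate.

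**Working it through.** **Inputs from the article**

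- Per-indicator level: 0.05, no adjustment stated (two-sided assumed).
- Patients: 150 planned, 10% loss, so 150 × 0.90 = 135.
- MACE rate: 151/1864 = 0.081, which reproduces the cited 8.1%.

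**The plan's own figure.** The calculated sample size of 125 is reproduced by the two-proportion formula with pooled variance under the null, for 0.05% versus 8.1% at two-sided 0.05. Power is not stated; 90% is assumed.

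n = [1.96 × √(2 × 0.04075 × 0.95925) + 1.2816 × √(0.081 × 0.919 + 0.0005 × 0.9995)]² / 0.0805² = (0.548 + 0.351)² / 0.00648 ≈ 125 per group.

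That compares ACS patients with healthy people. It does not size the analysis discussed here, which compares patients with and without MACE inside the cohort.

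**Derived counts (assumptions, with ranges)**

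- Events: 135 × 0.081 = 10.9, about 11. With no loss, 150 × 0.081 = 12.2. If MACE were 20% or 30%, there would be 27 or about 41.
- Indicators, all molecules on all subsets: 8 + 8 × 4 = 40.
- Indicators, with SIRPα on the five monocyte and macrophage subsets only and Tim-3 on the three T and NKT subsets only: 8 + 8 + 8 + 5 + 3 = 32.
- Indicators, as eight cell counts plus four levels: 12.
- More than 40 if the clinical variables are screened too.
- Events per candidate at 40: 10.9 / 40 = 0.27.

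**Closed form, independent null indicators.** P(at least one P<0.05) = 1 − 0.95^m:

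- m = 12: 0.46
- m = 20: 0.64
- m = 32: 0.81
- m = 40: 0.87, with 40 × 0.05 = 2.0 false positives expected
- m = 60: 0.95

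**Simulation of the whole chain, no marker associated with MACE.** Steps: t-test screen at 0.05; stepwise logistic regression by likelihood ratio (entry 0.05, removal 0.10, both assumed because the article gives none); AUC in the same patients; AUC of the same model in 2000 new subjects. There were 1000 runs per row.

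| Patients / events | Indicators | Correlation | Spurious model | Median apparent AUC |
|---|---|---|---|---|
| 135 / 11 | 40 | 0 | 87% | 0.77 |
| 135 / 11 | 40 | 0.5 in blocks of 5 | 78% | 0.75 |
| 135 / 11 | 40 | 0.8 in blocks of 5 | 67% | 0.73 |
| 150 / 12 | 40 | 0 | 87% | 0.76 |
| 135 / 11 | 20 | 0 | 61% | 0.72 |
| 135 / 11 | 8 | 0 | 33% | 0.71 |
| 135 / 11 | 60 | 0 | 96% | 0.81 |
| 135 / 27 | 40 | 0 | 86% | 0.69 |
| 135 / 41 | 40 | 0 | 87% | 0.67 |

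AUC in new subjects was about 0.50 in every row. In the first row the interquartile range of the apparent AUC was 0.71-0.82. Its final models held 1.7 predictors on average over all runs, and 70% of all runs reached an apparent AUC of at least 0.70.

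Backward elimination at 0.05 gave nearly the same result at 11 events: 88% and 0.77 with independent markers, 74% and 0.72 at a common correlation of 0.3. At 27 events it gave AUCs of 0.69 and 0.65. Simulated rates for 12 and 32 indicators were about 44% and 79%, close to the closed form.

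**The case against.** Several objections have force.

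- **The counts are not in the article.** It states neither 40 indicators nor 11 events. A reader might take both as facts of the plan, but they are derived. The Discussion describes SIRPα mainly on macrophages and Tim-3 as a T-cell exhaustion marker, so fewer combinations may be analysed. The cited 8.1% may not fit this composite, which includes symptom-defined recurrent angina, heart failure and any restenosis seen at repeat angiography. More events bring the spurious AUC down to 0.65-0.69, which is not impressive. This stands, and is why ranges are given. More events do not, however, reduce the chance of a false model.
- **Certainty is not supported.** A reader might infer that false predictors are bound to appear. At 40 indicators the chance is about 67-88%, and it falls with correlated or fewer indicators.
- **The stepwise algorithm is unspecified.** One might argue that Wald-based selection with so few events adds separation and inflated odds ratios. The article names no test, direction or threshold, so that claim cannot be pinned on it. The results above do not need it.
- **An analysis plan may exist.** Silence on multiplicity or internal validation is therefore not an error in itself. What can be challenged is the chain that the article does state.
- **The study is exploratory and non-interventional.** That argues against imposing a confirmatory hypothesis. It does not excuse an AUC and cut-off that look better than they are, given the hope of guiding clinical work.

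**Conclusion.** The concern holds in this form: the stated chain of unadjusted screening, stepwise selection and ROC in one cohort is likely to report false predictors with an optimistic AUC when no marker works.

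The size rests on two assumptions, about 40 indicators and about 11 events. With 40 indicators a spurious model appears in about 67-88% of null studies, depending on correlation; with 12 it appears in about 44%. The median apparent AUC is about 0.71-0.77 at 11 events for up to 40 indicators and 0.65-0.69 at 27 events, against a true 0.50. Screening the clinical variables as well would worsen this (96% and 0.81 with 60 independent indicators).

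The figures describe the case of no true association. They do not show that the study's markers are unrelated to MACE, only that this procedure could not reliably tell.

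**What to change.** 1. Replace the P<0.05 filter and stepwise step with a small model specified in advance, or with penalised regression (for example Firth, ridge or LASSO).
2. If data-driven selection is kept, repeat all of it, from screen to cut-off, in each bootstrap resample. Report the optimism-corrected AUC, sensitivity, specificity and cut-off performance with 95% confidence intervals.
3. Report the marker tests with Benjamini-Hochberg false discovery rate control, state how many indicators were tested, and label the results exploratory.
4. Optional: name one primary marker-cell pair before the outcome data are analysed. This would give one clean test, but an exploratory study need not adopt it.

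The cost is revised analysis wording and a little programming, with no extra patients, samples or follow-up. The reported AUC will probably be less favourable.

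### The only stated criterion for the ROC cut-off, lowest incidence of MACE, is not a valid optimum and should be replaced by a named rule

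*Protocol article*

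**What the plan says.** In the Statistical analysis section of the protocol article, stepwise logistic regression screens the indicators, and then "The receiver operating characteristic (ROC) analysis was used to analyze the selected predictors". The cut-off follows in one sentence: "The optimal cut-off point was found when the incidence of MACE was lowest by calculating the area, sensitivity and specificity under the curve". The second half of that sentence repeats the criterion almost word for word. Area, sensitivity and specificity are to be calculated, but the text does not say how they select a point. It also does not say whether incidence is to be lowest below the cut-off, above it or in the whole cohort. No other section defines a cut-off, and no numerical cut-off, sensitivity or specificity is given.

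**The concern.** An ROC cut-off is a choice between sensitivity and specificity. The incidence of MACE belongs to a group of patients, and minimising it involves no such choice. A rule that minimises incidence therefore has either no solution or a solution at one end of the marker's range.

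At stake is the threshold attached to each predictor of the primary outcome. An analyst who follows the sentence may report a cut-off that separates patients poorly. An analyst who sees that it cannot work will substitute another rule after the data are in, and the cut-off becomes a post hoc choice.

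**Working it through.** The plan has no cut-off figure to reproduce, so the check takes each possible reading of the rule in turn.

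**Inputs from the Sample size section**
- Event rate: "another study showed that 1 year MACE in ACS patients is 8.1%(151 of 1864"; 151/1864 = 0.081.
- Planned enrolment is 150. "Considering the 10% loss rate of follow-up" leaves 150 × 0.90 = 135 patients.
- Expected MACE: 135 × 0.081 = 10.9, about 11, leaving 124 without an event.

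**Assumptions (not in the document)**
- The marker is N(0,1) without MACE and N(d,1) with MACE, where d = √2 × Φ⁻¹(AUC). High values mean high risk.
- AUC is varied from 0.60 to 0.80. At 0.70, d = 0.742.

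**Reading 1: incidence in the cohort.** It is 11/135 = 8.1% whatever the threshold. The rule selects no cut-off.

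**Reading 2: incidence in the group below the cut-off (classed low-risk).** In the population, with p = 0.081,

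incidence below t = pΦ(t − d) / [pΦ(t − d) + (1 − p)Φ(t)].

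At AUC 0.70:

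| t | Incidence below t | Sensitivity | Specificity |
|---|---|---|---|
| 0.37 (Youden point) | 4.6% | 0.64 | 0.64 |
| −1 | 2.2% | 0.96 | 0.16 |
| −2 | 1.2% | 0.997 | 0.02 |
| −3 | 0.6% | 1.00 | 0.001 |

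Incidence keeps falling as t falls, so there is no interior minimum.

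In a sample, incidence is zero at every threshold at or below the lowest marker value in a MACE patient. In simulated cohorts of 135 with 8.1% MACE and AUC 0.65 to 0.80, a median of 19 to 45 thresholds tie at this minimum. The lowest tied threshold has a specificity of about 0.01. The highest, which is the most favourable, was simulated in 3000 data sets per AUC (124 non-events, 11 events):

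| Assumed AUC | Mean specificity at highest tied threshold |
|---|---|
| 0.60 | 0.14 |
| 0.70 | 0.23 |
| 0.80 | 0.37 |

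A higher event rate makes this worse. At AUC 0.70 the mean specificity is 0.13 with 27 events and 0.10 with 40.

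**Reading 3: incidence in the group above the cut-off.** In the population, incidence above t rises with t, so the minimum lies at the bottom of the range, where specificity is near zero. In a sample, incidence is also zero above the highest marker value in a MACE patient if any event-free patient lies there. In simulated cohorts of 135 with 8.1% MACE, the median result was sensitivity 0.00 with specificity 0.92 to 0.96 at AUC 0.65 to 0.75. At AUC 0.80 it was sensitivity 1.00 with specificity 0.008. Both are extremes.

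**Performance in new patients at AUC 0.70.** Thresholds chosen in each simulated cohort were evaluated in the population.

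| Rule | Sensitivity | Specificity | Youden index J |
|---|---|---|---|
| Reading 2, highest tied threshold | 0.92 | 0.23 | 0.15 |
| Maximum Youden index | 0.60 | 0.66 | 0.26 |

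The sensitivity of 0.92 agrees with theory: the expected share of new MACE patients below the lowest of 11 events is 1/12, and 1 − 1/12 = 0.917. The best J attainable in this model is 2Φ(0.742/2) − 1 = 0.29. At AUC 0.80 the corresponding J values are about 0.28 and 0.41.

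**In-sample values.** At AUC 0.70 the Youden rule shows an apparent J of 0.42, above the attainable 0.29. With 11 events, in-sample accuracy is clearly inflated.

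**The case against.** The strongest defence is that the sentence is a badly worded conventional rule. It mentions sensitivity and specificity, and the repeated clause looks like an editing slip and adds no emphasis. That is plausible, but the text names no such rule, and the remedy is the same either way: state the criterion. Nor is this a detail that an article leaves to a fuller document, because a criterion is given and it is the wrong one.

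Four stronger readings are tempting, and the document does not support them.
- **That the plan's rule produces poor specificity.** This follows only under Reading 2. The specificities in the simulation table also need a tie-break (the highest tied threshold) that the article does not give. The same tie-break is what makes the threshold depend on a single patient.
- **That the Youden index would do far better.** The in-sample comparison at AUC 0.70 (J of 0.42 against about 0.24) overstates the gain. In new patients the gap is 0.26 − 0.15 = 0.11.
- **That the rule is distinctively unstable.** At AUC 0.70 the threshold's standard deviation is about 0.57 under Reading 2 and 0.52 under Youden; at AUC 0.60 Youden is the less stable (0.70 against 0.57). The main cause is the small number of events, which a new criterion does not cure.
- **That the cut-off is put forward as a guide to practice.** The article expresses that hope for the results as a whole and does not attach it to the cut-off.

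It is also fair to say that the cut-off comes after the main aim of relating the cell markers to MACE, and that it changes no data collection, sample size or association test.

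**Conclusion.** Wrong as written; should-fix. The stated criterion selects no threshold if read literally, and on either group-specific reading it runs to an end of the marker's range. On none of the three readings does it weigh sensitivity against specificity. That conclusion needs no assumed AUC or event rate beyond a marker that carries some information.

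The sizes do rest on assumptions: a normal marker with equal variances, AUC of 0.60 to 0.80, and about 11 events from the cited 8.1% rate. The composite includes recurrent angina and heart failure, so the true rate may be higher. The direction was the same at 20% and 30% MACE.

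**What to change.** Replace the cut-off sentence in the Statistical analysis section with a named, prespecified criterion based on sensitivity and specificity. Suggested text: *The cut-off for each selected predictor is the marker value that maximises sensitivity + specificity − 1. The cut-off, sensitivity and specificity will be reported with bootstrap 95% confidence intervals and corrected for optimism.* If a rule-out threshold is wanted, fix the required sensitivity in advance and take the threshold that meets it.

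The optimism correction matters because in-sample values are inflated with about 11 events. The criterion should be settled before outcomes are analysed. The cost is a sentence or two of text and a routine resampling step, with no new data and no change to recruitment or follow-up.
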